**Observed feasibility**				
	Nonattempters	Participants consented and started a support program	Participants consented, but dropped out before starting a support program	Behavior
	Noncompleters	Participants started and completed a support program	Participants started a support program, but dropped out before the end of treatment	Behavior
	Low general engagement	Participants completed a support program and completed most of the sessions	Participants completed a support program, but did not complete most of the sessions	Behavior
**Patient-reported feasibility**				
	Low general engagement	Participants completed a support program and were highly engaged throughout	Participants completed a support program, but had low engagement throughout	PATT^b^ items
	Low homework engagement	Participants completed a support program and were highly engaged with homework	Participants completed a support program, but were minimally engaged with homework	Journal log and clinician report

^a^We have retained our original preregistered outcomes but are presenting them via an updated organization.

^b^PATT: Program Acceptability Tool for Telehealth.

**Table 3 table3:** Optimal and suboptimal outcome categories across acceptability metrics

Acceptability categories		Desired outcome	Undesired outcome	Outcome coding
**Patient-reported acceptability**				
	Low acceptability	Participants completed a support program and found the program fit to be highly acceptable based on their needs	Participants completed a support program, but found the program fit to have low acceptability based on their own needs	PATT^a^ total score
**Clinician-reported acceptability**				
	Low acceptability	Participants completed a treatment program, and their clinician rated the treatment program to be a good match based on the participant’s needs	Participants completed a treatment program, and their clinician rated the treatment program to be a poor fit based on the participant’s needs	Clinician rating
**Peer coach-reported acceptability**				
	Low acceptability	Participants were assigned a peer coach, and their peer coach rated WellCAST to be a good fit based on the participant’s needs	Participants were assigned a peer coach, and their peer coach rated WellCAST to be a poor fit based on the participant’s needs	Peer coach rating

^a^PATT: Program Acceptability Tool for Telehealth.

**Table 4 table4:** Optimal and suboptimal outcome categories across efficacy metrics

Efficacy categories		Desired outcome	Undesired outcome	Outcome coding
**Patient-reported efficacy**				
	Nonresponders	Participants initially demonstrated high needs (per the algorithm), completed a support program, and their needs decreased	Participants initially demonstrated high needs (per the algorithm), completed a support program, and their needs persisted	Algorithm data
	Undetected needs	Participants initially demonstrated low needs (per the algorithm), completed a support program, and their needs remained low	Participants initially demonstrated low needs (per the algorithm), completed a support program, and their needs increased	Algorithm data

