#### Compensation

Caregivers are paid US $100 for completing assessments. There are 5 sets of forms total, and the amount of compensation increases over time to maximize response (baseline: US $10; start of programs and mid support programs: US $15 each; end of programs: US $30; and follow-up: US $30). Participants are not compensated for time spent in support programs. Participants who are participating in the waitlist control receive compensation as they would if they participated in a support program. Payment is delivered using Amazon gift cards after participants complete each set of forms, and support programs are delivered free of charge.

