#### Initial Decision Tree Algorithm

The algorithm, decision nodes, and thresholds are all preregistered on OSF Registries before use to promote transparency, explainability, and interpretability. Support program assignments are based on clinical and lifestyle data provided by participants in the 2-week baseline period. For example, in algorithm 1, participants who report high levels of emotional dysregulation, depression, stress, or anxiety will be eligible for adult-focused mental health programs. Once eligible for adult-focused mental health programs, participants are assigned to either individually delivered acceptance and commitment therapy (ACT) or group-based dialectical and behavioral therapy (DBT) based on their initial data. Participants with higher emotional dysregulation scores are routed to DBT, whereas participants with below-threshold levels of emotional dysregulation are routed to ACT. This threshold was determined via multiple data sources. A primary aim of the study is to evaluate and optimize the efficacy of these algorithms, and we anticipate that support program assignment criteria will evolve following preplanned algorithm optimizations, as will be detailed in peer-reviewed manuscripts describing study results. The full descriptions of all decision nodes and thresholds for each iteration of the algorithm are available in algorithm preregistrations on OSF Registries. We also anticipate that further justification for the support program assignment will be discussed in the peer-reviewed manuscripts describing study results after the trial has concluded.

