#### Interim Data Analysis for Algorithm Optimization

At 2 prespecified intervals, we assess the feasibility, acceptability, and efficacy of the routing algorithm and, broadly, Project WellCAST, in promoting the well-being of caregivers of children with NGCs. Following the CASCADE method for an interdisciplinary “think tank” process, we will use multiple data sources to inform each iteration of the algorithm to optimize and enhance effective triaging for support program implementation [29]. Tables 2-4 detail the metrics of feasibility, acceptability, and efficacy that will be the focus of each think tank, including the desired and undesired outcomes associated with each. Across metrics, we are specifically interested in predicting which individuals will respond suboptimally to the project so that we can proactively minimize these challenges in future versions of the algorithm.

The think tank will be attended by multiple project interest-holders, including NGC caregivers, project staff, clinicians, biostatisticians, and trainees. Before the think tank, biostatisticians will complete preregistered analyses, which will be presented alongside participant feedback and project interest-holder surveys. During the think tank, we will generate a list of hypotheses for how the algorithm can be improved; this list will be narrowed through a systematic process of (1) ensuring each change is supported by more than 2 sources of information (quantitative data, qualitative data, NGC community input, and past literature), (2) evaluating technical feasibility, and (3) ensuring each change is aligned with NGC community priorities. The output of each think tank will be a manuscript submission that justifies specific changes to the algorithm, as well as a preregistration of the resulting optimized algorithm, which will be used to route the subsequent wave of participants to support programs.

**Table 2 table2:** Optimal and suboptimal outcome categories across feasibility metrics^a^.

Feasibility categories		Desired outcome	Undesired outcome	Outcome coding

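### Table 4 compares later need with the same baseline data that set need status, with no comparator, so regression to the mean alone would produce some responders and some undetected needs

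*Protocol article*

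**What the plan says.** Routing works on baseline data. Under Initial Decision Tree Algorithm the article states: "Support program assignments are based on clinical and lifestyle data provided by participants in the 2-week baseline period". It gives an example of a threshold: "Participants with higher emotional dysregulation scores are routed to DBT, whereas participants with below-threshold levels of emotional dysregulation are routed to ACT". The cut values are not printed; the article says "The full descriptions of all decision nodes and thresholds for each iteration of the algorithm are available in algorithm preregistrations on OSF Registries".

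Table 4 (Interim Data Analysis for Algorithm Optimization) uses the same classification to judge efficacy. In the patient-reported rows, the desired result for a high-need caregiver is "Participants initially demonstrated high needs (per the algorithm), completed a support program, and their needs decreased". The undesired result for a low-need caregiver, labelled undetected needs, is "Participants initially demonstrated low needs (per the algorithm), completed a support program, and their needs increased". Both are coded from the algorithm data, and neither row names a comparison group. Both are limited to people who completed a program, so waitlist caregivers do not enter while they wait.

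The same section makes Tables 2–4 the focus of two think tanks, each of which leads to a revised algorithm. The stated interest there is that "we are specifically interested in predicting which individuals will respond suboptimally to the project".

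**The concern.** A caregiver is called high need because a baseline score lies above a threshold. Part of that score is temporary: a bad fortnight or measurement error. On average that part will have faded by follow-up, with or without a program. The reverse holds for caregivers called low need. When the score that defines the group is also the starting point for judging change, the high group tends to fall and the low group tends to rise for reasons unrelated to the programs.

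Two readings could go wrong at the think tanks. The share of high-need completers who improve could be credited to the programs. And a model of who fails to respond, or who has undetected need, could partly be a model of where the baseline score lay relative to the cut-off. Because the think tanks exist to revise the algorithm, a metric that moves without any program effect is a poor guide unless a benchmark stands beside it.

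**Working it through.** The article prints no figure for this point, so there is nothing to reproduce. The check asks what the Table 4 categories would show if the programs had no effect.

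**Inputs**
- From the article: need status from the 2-week baseline data; a threshold rule; outcome coded from the same algorithm data; a minimum of 500 participants including 50 waitlist controls (Study Design).
- Assumed, because the article does not give them: the correlation ρ between baseline and follow-up need (0.5, 0.7, 0.9) and the share classed as high need (30%, with 16% and 50% as alternatives). The alphas quoted for the scales describe internal consistency, not stability over time.
- Model: baseline X and follow-up Y are standard bivariate normal with equal means and SDs and no treatment effect. One score stands in for what is really a rule with several inputs.

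**Mean change**

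E[Y − X | group] = (ρ − 1) × E[X | group].

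With 30% classed high, the cut-off is c = 0.524 SD and the normal density there is 0.348. Then E[X | high] = 0.348 / 0.30 = 1.16 and E[X | low] = −0.348 / 0.70 = −0.50. At ρ = 0.7 the high group changes by −0.3 × 1.16 = −0.35 SD and the low group by −0.3 × (−0.50) = +0.15 SD.

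**Crossing the cut-off**

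P(fall | high) = 1 − P(X > c, Y > c) / 0.30.
P(rise | low) = [0.30 − P(X > c, Y > c)] / 0.70, which equals P(fall | high) × 0.30 / 0.70. At ρ = 0.7: 0.365 × 0.30 / 0.70 = 0.156.

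**Results with zero program effect, 30% classed high**

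| | ρ = 0.5 | ρ = 0.7 | ρ = 0.9 |
|---|---|---|---|
| High need, fall below cut-off | 48% | 37% | 21% |
| Low need, rise above cut-off | 20% | 16% | 9% |
| High need, any decrease | 74% | 68% | 60% |
| Low need, any increase | 60% | 58% | 55% |
| Mean change, high (SD) | −0.58 | −0.35 | −0.12 |
| Mean change, low (SD) | +0.25 | +0.15 | +0.05 |
| Within 0.5 SD above cut-off, fall below | 57% | 50% | 36% |
| Within 0.5 SD below cut-off, rise above | 33% | 32% | 27% |

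Over ρ from 0.5 to 0.9 and high-need shares of 16% to 50%, 14–61% of the high group fall below the cut-off and 5–33% of the low group rise above it.

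**Where the artefact sits**

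This depends on the scoring rule, which the article does not print. If need is scored as above or below the threshold, misclassification concentrates near the cut-off: at ρ = 0.7, 32% of those just below it cross, against 16% of the whole low group. If change itself is scored, expected drift is (ρ − 1)X and is largest at the extremes. Those just below a cut-off that lies above the mean then drift down, not up: −0.08 SD on average at ρ = 0.7, with 46% increasing.

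**Precision of the waitlist benchmark**

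If 30% of 50 waitlist caregivers are high need, that is 15 people. For a 37% crossing rate the 95% half-width is 1.96 × √(0.37 × 0.63 / 15) = 0.24, or about 24 percentage points.

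**The case against.** The article is a condensed account. Thresholds, analytic plans and think-tank procedures are deferred to OSF, and preregistered analyses precede each think tank. Those analyses may already adjust for baseline or use a comparator, and this cannot be seen here. That stands as a limit on the point. But the article does print the categories and their coding, and the objection is to that printed definition.

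The design has usable comparators. The algorithm's ranked list is generated before the first randomization (Routing Procedures), so quasi-random caregivers in waves 1–2 can be given the same need status and should show the same expected regression. The waitlist contributes identical data so that efficacy can be evaluated. This also stands: the trial has comparators, and Table 4 does not use them. In wave 3 everyone receives algorithm 2, so there is no concurrent quasi-random arm.

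Each algorithm change must be supported by more than two of four kinds of evidence. Table 4 rates therefore cannot move a threshold alone, but they can still count as the quantitative source.

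The size is assumed. Baseline EMA allows up to 3 × 14 = 42 prompts, and averaging them may raise stability. At ρ = 0.9 the crossing rates drop to 21% and 9%, which is smaller but not negligible.

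A reader might infer more than the documents support:
- That Table 4 scores raw change. No scoring rule is printed, and its wording about needs persisting or staying low can equally be read as threshold status.
- That the clinician and coach rows share the flaw to the same degree. They are coded by the CGI, which includes a direct rating of improvement, and nothing says that the CGI drives routing.
- That the think tanks will be led to lower thresholds. This is conjecture.

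**Conclusion.** The point holds for the patient-reported rows of Table 4. As printed, they judge later need against the baseline that defined it, among completers and without a comparator, so regression to the mean adds to both the responder and the undetected-needs categories. The direction holds for any baseline-to-follow-up correlation below 1. The size rests on an assumed correlation and an assumed high-need share; with 0.5–0.9 and 30%, it is 21–48% of the high group and 9–20% of the low group crossing the cut-off with no program effect.

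This is a worthwhile, low-cost improvement to an interim metric that informs algorithm revision. A reader might infer that it undermines the trial's efficacy results. It does not: these categories are separate from the listed primary outcomes and from the randomized comparison of algorithm 1 with quasi-random assignment.

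**What to change.** 1. Beside each patient-reported Table 4 rate, report the same rate or mean change in waitlist caregivers at the same baseline need. This is the no-program benchmark.
2. For waves 1–2, also report it in quasi-random caregivers with the same algorithm-computed need. They too receive programs, so this is a benchmark for routing, not for program effect.
3. Adjust models that predict nonresponse or undetected need for the continuous baseline score, so that position relative to the cut-off is not mistaken for a predictor.
4. State that unadjusted Table 4 rates do not count as the quantitative source for a threshold change.
5. Say whether need at follow-up is scored by threshold status or by amount of change.

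The cost is analysis wording and modest programming on data already collected. The limits should be stated: about 50 waitlist caregivers give an imprecise benchmark, wave 3 has no concurrent quasi-random arm, and the Table 4 rows contain completers only, so comparison with the waitlist is not fully like for like.

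Scoring change from a second pre-program measurement is optional. The Compensation section lists a separate set of forms ("start of programs and mid support programs: US $15 each"), but Study Procedures describes the preprogram forms together with the baseline phase, and the measurement schedule is in a figure not available here. This would help only if those forms repeat the routing scales and are separate in time from baseline.

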**Clinician-reported efficacy**				
	Nonresponders	Participants initially demonstrated high needs (per clinician), completed a support program, and their needs decreased	Participants initially demonstrated high needs (per clinician), completed a support program, and their needs persisted	CGI^a^
	Undetected needs	Participants initially demonstrated low needs (per clinician), completed a treatment program, and their needs remained low	Participants initially demonstrated low needs (per clinician), completed a support program, and their needs increased	CGI
**Peer coach-reported efficacy**				
	Nonresponders	Participants initially demonstrated high needs (per coach), completed a support program, and their needs decreased	Participants initially demonstrated high needs (per coach), completed a support program, and their needs persisted	CGI
	Undetected needs	Participants initially demonstrated low needs (per coach), completed a support program, and their needs remained low	Participants initially demonstrated low needs (per coach), completed a support program, and their needs increased	CGI

^a^CGI: Clinical Global Impression Scale.

Additional information about the think tank and CASCADE method procedures is available on OSF Registries and is being published via separate manuscripts that detail the theoretical impetus, process, and outputs of the think tank process.

## Results

The study was approved by the Purdue University IRB on March 3, 2023. The study began its first wave on August 5, 2024, and concluded on January 26, 2024. As of May 31, 2024, 586 participants have completed the virtual prescreening survey. Of those participants, 367 (62.6%) completed screening interviews, and 285 (48.6%) consented to the baseline phase of the study. Figure 3 depicts a CONSORT (Consolidated Standards of Reporting Trials) diagram for additional details regarding initial study enrollment. Data collection is expected to be completed in September 2025, with final study results expected by September 2026; however, the manuscripts will be submitted for publication as data are unmasked across preplanned trial phases.

**Figure 3 figure3:**
[figure not shown]
CONSORT (Consolidated Standards of Reporting Trials) flowchart for overall study enrollment as of May 31, 2025. LTFU: loss to follow-up.

## Discussion

### Principal Findings

Precision health methods have the potential to improve the feasibility and efficacy of tele–mental health programs for high-need populations, including and beyond NGC caregivers. Project WellCAST tests whether a precision health decision tree algorithm can be developed and used to improve clinical outcomes among NGC caregivers engaging in brief, 12-week, evidence-based support programs. We plan to disseminate trial results through multiple avenues, including publication in peer-reviewed journals, conference presentations, community-based webinars, and other methods as appropriate. It is anticipated that our results will improve understanding of the personal and clinical factors that may predict suboptimal outcomes. If successful, we anticipate Project WellCAST will provide a model for rapidly virtually assessing and triaging populations in need of tele–mental health care, including during future public health emergencies, such as the COVID-19 pandemic.

Several innovations uniquely situate Project WellCAST to contribute to the precision health and psychiatry literatures. First, we use digital health approaches that leverage smartphone-based data to monitor daily fluctuations in symptoms—rather than one-time clinical intake self-report data—providing a more detailed topography of initial patient needs and more sensitive metrics of acute, real-world change over time.

We also leverage community-academic partnerships that provide a scalable, cost-effective model for deploying community-centered interventions while simultaneously training the next generation of mental health providers to deploy digital evidence-based interventions with high-risk populations. To do this, we have aligned multiple digital support programs to a 12-week simultaneous delivery framework, providing a foundation for integrative support programs that can be individualized to families yet delivered with cohesion by trainees.

An additional innovation is that we incorporate extra support elements that we anticipate will boost clinical outcomes for participants who may face further barriers to treatment. For example, we include program options for caregivers experiencing comorbid racial trauma, led by highly qualified experts in the needs of minority families. We leverage community-based partnerships with peer support coaches to deploy evidence-based motivational interviewing protocols to boost program completion and efficacy, while simultaneously maximizing the involvement of patient communities.

These innovations are timely and necessary for NGC caregivers during and after the COVID-19 pandemic; however, this project also has the potential to inform improvements to the long-term landscape for how digital health programs are assigned and deployed far beyond this specific population or public health crisis. Indeed, the high baseline stress and scheduling constraints experienced by NGC caregivers make them an ideal user development group for innovating support program networks that are feasible and acceptable to variety of future users, including those experiencing trauma similar to what was experienced during the pandemic (eg, first responders, teachers, and frontline nurses) or full-time caregivers for other patient groups (eg, patients with dementias). In other words, our model, if successful, can be rapidly adapted and scaled to meet the needs of countless special populations as part of both general standard care and crisis response efforts.

Our study may also inform more cost-effective and sustainable clinical trial practices for several reasons. First, the design of the trial is built on community-academic partnerships, where support programs are deployed by graduate student clinicians with appropriate oversight from licensed supervisors. By engaging student-trainees to deploy support programs, we have minimized the overall cost of deploying programs while simultaneously providing high-quality training opportunities, including necessary clinical hours for licensure eligibility, for the next generation of clinicians. More broadly, our study aims to inform how to minimize mismatches between patient needs and provider offerings, which can reduce unnecessary costs associated with ineffective programming and patient attrition. Appropriately matching patients to support programs can save time, money, and frustrations for both the mental health provider and the patient, supporting sustainability and efficiency.

Project WellCAST was also designed to be intentionally *noninnovative* in 1 important way—the support programs being tested are already evidence-based and widely available to the general population. In other words, it is possible that Project WellCAST’s 2-week baseline data collection procedure and associated precision health algorithm can improve the field’s understanding of how best to route patients to already-available programs in their communities, in line with current directions in precision mental health [14]. For example, our efforts to identify “suboptimal responders” may inform which practical lifestyle factors indicate or counterindicate telehealth-based support programs, which patients may benefit most from additional coaching support, and whether a given patient should be offered mental health support versus parenting coaching. Additional studies on the generalizability of our final decision tree algorithm will be an important interim step toward this goal.

It is important to highlight that we expect Project WellCAST to be a strong match for some participants and a potentially poor match for others. Although telehealth has rapidly expanded in the wake of the COVID-19 pandemic, we and others have continued to caution that telehealth alone will not address the preexisting demographic health disparities that continue to persist across a variety of fields [16]. Our hope is that Project WellCAST can generate the data and results necessary to determine the contexts in which telehealth is most useful [6]. These contributions could be highly clinically relevant for other caregiver groups (eg, other special needs, severe mental illness, and older adults), including those experiencing race-related stress or trauma.

